## Methods

### Phase I: intervention rollout and implementation trial

#### Hypotheses

Compared with pre-intervention, a larger proportion of post-operative radical prostatectomy patients who are at high risk of recurrence (have extracapsular extension, seminal vesicle involvement or positive surgical margins) treated in hospitals after implementation of the intervention will receive a referral to radiation oncology for consideration of adjuvant radiotherapy or referral to the RAVES trial [Radiotherapy Adjuvant Vs Early Salvage (Protocol Number: TROG.08.03); see the ‘RAVES Trial’ subsection for details].

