### Design

This will be a phased randomised cluster trial with phased introduction of a clinical network led organisational intervention in nine hospitals over 10 months. The order in which hospitals will receive the intervention will be determined randomly using a stepped wedge study design (see Figure 3). This design, originally developed for community studies, has more recently been applied to health service interventions in hospitals [67] and has the following advantages: provides a control comparison where geographic controls are not possible; allows all hospitals in the clinical network with multidisciplinary teams to take part in the intervention; enables the intervention to be tested within the parameters of real-world allocation of clinical network resources with a phased roll out of the hospital-based intervention; and complies with the Cochrane Effective Practice and Organisation of Care Group’s consensus statement about study designs of sufficient quality to be included in systematic reviews. This study will be conducted and reported in accordance with the CONSORT statement for the reporting of pragmatic trials [68,69].The intervention will be rolled out across the nine hospitals in five steps of two-month blocks from December 2013 to September 2014. Throughout the study, hospitals will either be in the active implementation (intervention) or passive (control) phase (see Figure 3). Eligibility criteria for inclusion are public hospitals: with a urology multidisciplinary team (MDT) comprising specialists, nurses, and allied health professionals; and that are members of the ACI Urology Clinical Network and have a urologist who will act as the Clinical Leader for that site. All urologists who are members of the urology multidisciplinary team at intervention hospitals will be eligible for inclusion (n ≈ 4 – 10 urologists per hospital).

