### Data analysis

The primary analysis will be conducted at the individual patient level using a generalized estimating equations (GEE) approach to account for repeated outcome observations within clusters (urologists and MDTs). The dependent variable for this analysis will be referral to a radiation oncology service for adjuvant radiotherapy or enrolment into the RAVES trial (versus no referral) for each prostate cancer case. The exposure variable will be the intervention status (pre versus post) of the hospital at the time of the post-prostatectomy consultation. Other independent variables will be added to the model if they are shown to be independently associated with radiotherapy referral and/or their inclusion in the model changes the linear coefficient of the intervention effect by more than 20% in absolute value. Analysis to determine the extent to which changes in urologists’ knowledge, attitudes and beliefs (Phase II) mediated any changes in referral patterns will be assessed by including clinicians’ change scores in the GEEs.

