### Sample size and statistical power

Based on estimates from the NSW Central Cancer Registry and Medicare claims data we estimate that 3,517 NSW men will have a radical prostatectomy in 2013. Approximately 1,618 (46%) of these will be performed in the nine hospitals with urological MDTs participating in the ACI Urology Clinical Network according to linked cancer registry and hospital data for all NSW men diagnosed with prostate cancer. Assuming no major change has occurred in this distribution, there will be 1,348 radical prostatectomies over the 10 months of this trial. Of these, 20 to 50% or 270 to 671 men will be at ‘high risk’ [22-25]. The stepped wedge design is relatively insensitive to variations in the intracluster correlation (ICC) as a consequence of its efficient use of within-cluster and between-cluster information and has little impact on the study's power. However, based on the best available information, we estimate that the ICC for use of radiotherapy will be between 0.09 and 0.15 [72].

The most recently available data indicate 10% of high-risk men receive radiotherapy after surgery in NSW [33]. With the release of the Australian Cancer Network Clinical Practice Guidelines and the commencement of the RAVES trial we estimate that at the commencement of our trial, administration of radiotherapy following surgery will have increased to 15% to 20% of high-risk patients. Our stepped wedge study design with nine clusters, six time intervals (including the pre-intervention control step) and ICCs of 0.09 to 0.15 will have at least 80% power to detect an increase in referral to a radiation oncologist from 15% to 35%, or 20% to 40% if a minimum of 30% of patients are at high risk, and from 20% to 35% if at least 50% of prostate cancer cases are at high risk.

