### Data collection

A quantitative study of urologists will be conducted using a questionnaire to assess knowledge, beliefs, social influences, attitudes and motivation at three time points: baseline (pre-intervention); six months after the roll-out of the intervention; and at the end of the study (n ≈ 4 – 10 urologists per hospital). The survey is tailored to the intervention, uses previously identified domains (knowledge, beliefs, motivation, social influences), constructs, and generic questions to investigate the implementation of evidence-based practice [48], and is modelled on questions developed for other clinical conditions [75]. The measures using Likert scales have been developed through pilot testing and their feasibility and reliability will be assessed as part of the data collection in accordance with best practice [76]. Questions are consistent with those used in the baseline nationwide survey of urologists to enable comparison between groups. These surveys produce continuous scores for knowledge, beliefs, social influences, attitudes, and motivation at the clinician level that will be averaged for each hospital at each time point.

A follow up nationwide survey of urologist members of the Urological Society of Australia and New Zealand (USANZ) (n ≈ 370) will be conducted to determine whether urologists’ attitudes shifted locally/nationally without intervention.

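### The primary GEE does not pre-specify calendar time, so in this stepped wedge a substantial share of any background rise in referral would count as intervention effect

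*Protocol article*

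**What the plan says.** All references are to the protocol article.

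- **Data analysis (Phase I).** The primary analysis is a patient-level GEE with clustering by urologist and MDT. Its exposure is defined as follows: "The exposure variable will be the intervention status (pre versus post) of the hospital at the time of the post-prostatectomy consultation". Further terms are conditional: "Other independent variables will be added to the model if they are shown to be independently associated with radiotherapy referral", and/or if including them "changes the linear coefficient of the intervention effect by more than 20% in absolute value". Calendar month, period and step are not mentioned.
- **Hypotheses (Phase I).** The contrast has the same form: "Compared with pre-intervention, a larger proportion of post-operative radical prostatectomy patients who are at high risk of recurrence".
- **Design.** What is randomised is the roll-out sequence: "The order in which hospitals will receive the intervention will be determined randomly using a stepped wedge study design". Nine hospitals start in five two-month steps from December 2013 to September 2014.
- **Data windows.** Baseline cases run from January to November 2013 (Data collection, Phase I). Records are reviewed for 12 months after each hospital's education session, ending in September 2015 (Figure 3 legend).
- **Sample size and statistical power.** The earlier radiotherapy rate is 10%, but "we estimate that at the commencement of our trial, administration of radiotherapy following surgery will have increased to 15% to 20% of high-risk patients". Power of at least 80% is claimed for nine clusters, six time intervals and ICCs of 0.09 to 0.15.
- **Phase II, Data collection.** A follow-up national survey will look at whether urologists' "attitudes shifted locally/nationally without intervention". It measures attitudes, not referral, and is not described as an input to the primary model.

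**The concern.** In a stepped wedge every hospital moves from control to intervention as time passes, so later cases are more often intervention cases. The random order allows the intervention to be separated from a time trend only if the model conditions on time. The stated model guarantees no such term. The data windows widen the gap, because the baseline months have no intervention hospitals and the months after roll-out have no control hospitals.

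The protocol gives its own grounds for expecting background change: release of the guidelines and the start of the RAVES trial. If referral was rising anyway, the primary estimate is biased upward, and an ineffective intervention could be declared effective.

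**Working it through.** **1. The plan's power figure.**
From the sample size section: 1,348 prostatectomies in 10 months, high-risk share 30% or 50%, nine hospitals, six intervals, ICC 0.09 to 0.15. Assumed: steps of 2, 2, 2, 2, 1; equal hospital sizes; two-sided alpha 0.05; variance s² = p(1−p) at the midpoint of the two rates. With the cases spread over 9 × 5 = 45 hospital-periods, n = 404.4/45 = 9.0 (30%) or 674/45 = 15.0 (50%).

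The covariance of a hospital's six period means is V = (1−ρ)(s²/n)I + ρs²J. The SE of the effect is the square root of the last diagonal element of (ΣZ′V⁻¹Z)⁻¹. Z holds intervention status plus either six period effects or an intercept only. Power = Φ(δ/SE − 1.96).

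| Scenario | SE, with periods | Power | SE, no periods | Power |
|---|---|---|---|---|
| 15% to 35%, 30% high risk | 0.0651–0.0641 | 87–88% | 0.0411–0.0400 | >99% |
| 20% to 40%, 30% high risk | 0.0689–0.0678 | 83–84% | 0.0435–0.0423 | >99% |
| 20% to 35%, 50% high risk | 0.0529–0.0517 | 81–83% | 0.0330–0.0321 | >99% |

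In each SE pair the first value is for ICC 0.09 and the second for 0.15. Example: 0.20/0.0651 − 1.96 = 1.11, and Φ(1.11) = 0.867.

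If the same cases are spread over 9 × 6 = 54 hospital-periods (n = 7.5 or 12.5), time-adjusted power is 81–82%, 76–77% and 74–76% in the same order. Without periods it stays above 98%.

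**2. Calendar gap.**
Number January 2013 as month 1 and let each hospital start in the first month of its block (s = 12, 14, 16, 18, 20). Control months are 1 to s−1, with mean s/2. Intervention months are s to s+11, with mean s+5.5. The within-hospital gap is s/2 + 5.5, which runs from 11.5 to 15.5 months.

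Pooled over hospitals:
- Control mean: (2×66 + 2×91 + 2×120 + 2×153 + 190)/(2×11 + 2×13 + 2×15 + 2×17 + 19) = 1050/131 = 8.0.
- Intervention mean: (2×17.5 + 2×19.5 + 2×21.5 + 2×23.5 + 25.5)/9 = 189.5/9 = 21.1.
- Gap: 13.0 months.

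**3. Bias with no true effect and a linear trend.**
- *Six-interval design, intervals numbered 0 to 5.* Under independence the mean interval is 105/29 = 3.62 for intervention and 30/25 = 1.20 for control. The share of the total rise credited to the intervention is (3.62 − 1.20)/5 = 48%. With exchangeable weighting at ICC 0.09 to 0.15 it is 58–59%. A 5-point rise over the design gives +2.4 to +3.0 points, and a 10-point rise gives +4.8 to +5.9.
- *Full data window.* 2 × 13.0/12 = 2.2 points at 2 points a year, and 5 × 13.0/12 = 5.4 points at 5 points a year. Exchangeable weighting takes the latter to about 5.6.

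**4. False-positive rate.**
Simulated over the full window with a logistic GEE, nine hospital clusters, about 4.5 high-risk men per hospital-month, no true effect, and time never added:

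| Trend (assumed) | Uncorrected robust SE | Small-sample-corrected SE |
|---|---|---|
| none | 10% | 4% |
| 2 points/year | 23% | 9–10% |
| 5 points/year | 63% | 37–39% |

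The last column isolates the trend. The uncorrected column already starts at 10% because nine clusters are too few for an uncorrected sandwich variance.

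**5. Check of the remedy.**
On the six-interval design with no true effect (ICC 0.09, 9 men per cell) and rises of 5 and 10 points, the mean estimated effect was 0.028 and 0.056 without periods. With periods it was 0.000 and 0.001.

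**The case against.** **The covariate rule can admit time.** The rule has no closed list, and dates of surgery are collected. In a simulation with no true effect, adding linear month moved the coefficient by more than 20% in 92% of trials at 2 points a year and in 94–95% at 5 points. So if time is tried, it would usually enter. This stands as far as it goes: time is not excluded. But nothing says it will be tried, and the rule protects less when the intervention works. With a true 15-point effect and a 2-point trend, the expected change is 2.2/17.2 = 13%, below the threshold, and time entered in only about half of trials.

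**The evidence for a trend is indirect.** The rise from 10% to 15–20% is placed before the trial, is tied to two events, and concerns radiotherapy given, not referral. This stands. It makes a continuing trend plausible but does not show one, and the document gives no rate of rise during the trial.

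**Randomisation still does some work.** A reader might infer that the analysis is an uncontrolled before-after comparison that absorbs every point of secular rise. The documents do not support that. During roll-out, hospitals in random order are under both conditions at once, and the pooled GEE uses part of that contrast. What is lost is the use of the random order to separate intervention from time.

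**The power statement is not proof of a mismatch.** A reader might infer that the trial was powered for a different model. But a claim of at least 80% is also met by a model with 99%. The closeness to 80% with period effects is suggestive only, since method, alpha and step split are assumed.

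**Conclusion.** The point holds: the primary model guarantees only pre/post status, and control of the main confounder in this design is left to a post-hoc rule. Without a time term, about half to 60% of a rise over the six-interval design, or roughly one year's rise over the full window, is credited to the intervention. For an assumed 2 to 5 points a year this is about 2 to 5.5 points against the 15 to 20 point target. The corresponding false-positive rate is 9–10% to 37–39%.

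These sizes rest on the assumed trend, the 2, 2, 2, 2, 1 split, equal hospital sizes and time never being added. The higher rates of 23% and 63% should not be attributed to the trend alone, because they include the small-cluster variance problem. The stated power is consistent with a time-adjusted model (81–88% with about 9 or 15 men per hospital-period), but this is an inference.

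The matter should be corrected before analysis because it bears on the primary estimate.

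**What to change.** In the Phase I Data analysis section, state that calendar time is a fixed part of the primary GEE, exempt from the association and 20%-change rule. Use a form that nine clusters can support. One option is the six design intervals, with the baseline months grouped and the post-roll-out months grouped; another is a low-order trend. A separate effect for every two-month block from January 2013 to September 2015 would mean about 16 period terms (33/2), too many for a robust GEE with nine clusters. Grouping costs little, because the baseline and post-roll-out months contain no concurrent comparison between conditions. Specify a small-sample-corrected SE. Keep the unadjusted pre/post contrast as descriptive only.

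The cost is precision. In the 15% to 35% scenario at ICC 0.09 the SE of the effect rises from about 0.041 to about 0.065. The stated 80% should be rechecked under the time-adjusted model. With midpoint variance it holds if the 1,348 cases fill 45 hospital-periods, but drops to about 74–77% for 20% to 40% and 20% to 35% if they are spread over all six intervals. No new data collection is needed, since dates of surgery are already extracted.

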### Sample size and statistical power

Based on estimates from the NSW Central Cancer Registry and Medicare claims data we estimate that 3,517 NSW men will have a radical prostatectomy in 2013. Approximately 1,618 (46%) of these will be performed in the nine hospitals with urological MDTs participating in the ACI Urology Clinical Network according to linked cancer registry and hospital data for all NSW men diagnosed with prostate cancer. Assuming no major change has occurred in this distribution, there will be 1,348 radical prostatectomies over the 10 months of this trial. Of these, 20 to 50% or 270 to 671 men will be at ‘high risk’ [22-25]. The stepped wedge design is relatively insensitive to variations in the intracluster correlation (ICC) as a consequence of its efficient use of within-cluster and between-cluster information and has little impact on the study's power. However, based on the best available information, we estimate that the ICC for use of radiotherapy will be between 0.09 and 0.15 [72].

The most recently available data indicate 10% of high-risk men receive radiotherapy after surgery in NSW [33]. With the release of the Australian Cancer Network Clinical Practice Guidelines and the commencement of the RAVES trial we estimate that at the commencement of our trial, administration of radiotherapy following surgery will have increased to 15% to 20% of high-risk patients. Our stepped wedge study design with nine clusters, six time intervals (including the pre-intervention control step) and ICCs of 0.09 to 0.15 will have at least 80% power to detect an increase in referral to a radiation oncologist from 15% to 35%, or 20% to 40% if a minimum of 30% of patients are at high risk, and from 20% to 35% if at least 50% of prostate cancer cases are at high risk.

### Staff training and evaluation

Primary and secondary outcomes can be measured reliably through clinical data collection and this method has been used previously [33,73,74]. Research assistants conducting the medical record review will be trained and we will conduct a 10% blinded re-review to assess inter-rater reliability.

### Phase II: identify mechanisms of provider and organisational change

#### Design

‘Before and after’ mixed methods study to measure knowledge, attitudes, process, and explanatory variables.

### Urologists’ knowledge and attitudinal outcomes

#### Hypotheses

Compared with pre-intervention measures, urologists post-intervention will have: increased knowledge about the evidence for appropriate adjuvant radiotherapy for high-risk prostate cancer patients after radical prostatectomy and the associated risks and benefits of treatment; and more positive attitudes towards the need for referral to radiation oncology as a means to support fully-informed patient decision making.

### Data collection

A quantitative study of urologists will be conducted using a questionnaire to assess knowledge, beliefs, social influences, attitudes and motivation at three time points: baseline (pre-intervention); six months after the roll-out of the intervention; and at the end of the study (n ≈ 4 – 10 urologists per hospital). The survey is tailored to the intervention, uses previously identified domains (knowledge, beliefs, motivation, social influences), constructs, and generic questions to investigate the implementation of evidence-based practice [48], and is modelled on questions developed for other clinical conditions [75]. The measures using Likert scales have been developed through pilot testing and their feasibility and reliability will be assessed as part of the data collection in accordance with best practice [76]. Questions are consistent with those used in the baseline nationwide survey of urologists to enable comparison between groups. These surveys produce continuous scores for knowledge, beliefs, social influences, attitudes, and motivation at the clinician level that will be averaged for each hospital at each time point.

A follow up nationwide survey of urologist members of the Urological Society of Australia and New Zealand (USANZ) (n ≈ 370) will be conducted to determine whether urologists’ attitudes shifted locally/nationally without intervention.

### Process outcomes

#### Research question

Was the intervention implemented as intended?

### Data collection

The date of commencement of the intervention will be noted as the day the Urologist Clinical Leader within each site facilitated the educational intervention session. Agendas and minutes of subsequent MDT meetings will be reviewed using a method developed by members of the investigator team [77] to assess: numbers attending the meeting; frequency of mentioning the study; discussion of cases flagged by pathology; presentation of medical record review feedback; and changes in hospital practice as indicators of sustained interest in the intervention and organisational process changes.

### Research questions

1. Why did or did not the intervention result in evidence-based care?

2. Why was or was not the intervention implemented or sustained in hospitals?

### Data collection

1. Qualitative semi-structured interviews with Clinical Leaders at the end of the study to feedback study results and explore the reasons for them (n = 9).

2. Qualitative semi-structured telephone interviews, informed by feedback from Clinical Leaders, with urologists in the nine intervention hospitals at the end of the study to feedback study results and further explore the reasons for them (n ≈ 4 – 10 urologists per hospital).

### Data analysis

Survey data will be analysed using bivariable methods (means, t-tests and ANOVA for normally distributed continuous data; medians and non-parametric tests for non-normally distributed continuous data; and proportions and chi-squared tests for categorical data).

Semi-structured interview data will be analysed thematically using a matrix-based framework to organise data according to the theoretical framework used for the intervention design to identify why changes did or did not happen in the hospitals and why the intervention did or did not result in improved care.

### Research governance

The study has been approved by Royal Prince Alfred Research Ethics Committee (ID: X12-0388 & HREC/12/RPAH/584). Site-specific approval (SSAs) from the research governance office at each of the nine participating hospitals has been obtained. Site-specific approval from Cancer Council NSW ethics committee has been granted to cover data collection, storage and analysis at Cancer Council NSW.

## Trial status

The intervention and data collection phase of the study commenced in December 2013.

## Discussion

Clinical networks such as those established by the NSW Agency for Clinical Innovation are increasingly being viewed as an important strategy for increasing evidence-based practice in Australia and other countries. This interest in clinical networks is accompanied by significant investment in them but few studies have directly tested their effectiveness in driving implementation initiatives. To the authors’ knowledge, this study will be one of the first randomised controlled trials to test the effectiveness of clinical networks to lead changes in clinical practice in hospitals treating patients with high-risk cancer and improve evidence-based care.

